### Interim analyses

The trial’s steering team will assess accrued adverse events at 10% and 25% of target patient recruitment (126 and 315 patients). The DSMB will review accrued data related to treatment separation (MAP deficit over time) and serious adverse events in both arms after enrolment of 630 participants (50% of the planned sample size). An additional analysis of the primary outcome measure of all-cause 14-day mortality will also be performed during this interim analysis. The study team and the DSMB will remain blinded to the group allocations. Arbitrary dummy group labels, e.g. “A” “B”, will be randomly assigned to the study groups for the interim analysis of the primary outcome variable and different labels, e.g. “G”, “F”, will be assigned to study groups for the analysis of treatment separation. The trial will not be stopped for futility. Following the review of safety events, the DSMB will be required to make a consensus recommendation regarding continuation, modification, or early termination of the trial. In case a consensus decision is unable to be reached, then the DSMB can request an additional interim analysis for further data.

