### Safety assessment

Adverse events and serious adverse events will be defined according to standard regulatory criteria. Site investigators and research coordinators will prospectively collect safety data through daily review of medical records and direct communication with treating clinicians. The severity, seriousness and causality of each event will be assessed by the local investigator. Prespecified adverse events that will be reported besides death within 28 days of randomisation in hospital are atrial arrhythmia, ventricular arrhythmia, mesenteric ischemia, myocardial ischemia, Takotsubo cardiomyopathy, renal failure requiring RRT, bilateral digital ischemia, cardiac arrest, ischemic stroke and haemorrhagic stroke (Table 4). Additional adverse events defined as potentially or causally related to the study intervention or are otherwise of concern in the judgement of treating clinician will also be recorded. In keeping with established practice of reporting serious adverse events in critical care trials, those events that are deemed part of the natural course of the primary illness or expected complications of the critical illness are not required to be reported [16, 17]. Serious adverse events meeting reporting criteria will be submitted to the coordinating centre within 24 h of site awareness and reported to the relevant human research ethics committees.

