### Oversight and monitoring

This RCT will be coordinated by the clinical trials unit at Hunter Medical Research Institute. The trial management group comprises the chief investigator, project manager and clinical trials unit manager, who are responsible for the day-to-day conduct of the trial, including protocol compliance, site coordination and data quality monitoring. The trial steering group comprising of the chief investigator, medical co-investigators and project co-managers oversees trial governance and ensures the study is conducted in accordance with Good Clinical Practice. The trial steering group will conduct regular weekly or bi-weekly meetings. Any protocol variation will be duly approved by relevant regulatory bodies and communicated to all participating sites and collaborators.

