### Data safety and monitoring board

The Data Safety Monitoring Board (DSMB) for this trial comprise of three members with scientific expertise in clinical aspects of the patient population being studied, clinical trial conduct, biostatistics and methodology, and who will serve in an individual and independent capacity, free of any professional, intellectual, financial or emotional conflicts of interest in relation to the REACT SHOCK RCT and will provide their expertise and recommendations to the REACT SHOCK investigators. The DSMB members will be objective and unbiased in their assessment of safety and efficacy data provided to them periodically during the conduct of this study.

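### The blinded DSMB gets interim mortality and treatment separation under different labels with no stated key, so it could see a mortality difference without its direction

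*Protocol article*

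**What the plan says.** The Interim analyses section of the protocol article schedules these reviews.

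- **126 and 315 patients:** the "steering team will assess accrued adverse events at 10% and 25% of target patient recruitment". Whether these reviews are pooled or by arm is not stated.
- **630 patients:** the DSMB reviews treatment separation, described as MAP deficit over time, and "serious adverse events in both arms after enrolment of 630 participants (50% of the planned sample size"). 14-day mortality is analysed at the same look.

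On masking, the section says "The study team and the DSMB will remain blinded to the group allocations". Mortality is to carry arbitrary, randomly assigned labels such as A and B. Different labels, such as G and F, "will be assigned to study groups for the analysis of treatment separation". The labels for serious adverse events are not given.

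After its safety review the board must reach a consensus recommendation to continue, modify or terminate early. If it cannot, it may ask for a further interim analysis. The section mentions no release of the code and no link between the two label sets.

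The Data safety and monitoring board section expects members to be "objective and unbiased in their assessment of safety and efficacy data provided to them periodically".

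**The concern.** A recommendation on early termination depends on which arm is doing worse. More deaths under individualised targets is a safety signal. More deaths under standard care is the benefit that the trial was designed to find. Under labels that the board cannot decode, the two look the same.

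The second label set adds to the problem. With a single set, the MAP data would probably show which column is the individualised arm, and the mortality table could then be read. Separate sets have no evident purpose other than to prevent this. They also stop the board from relating deaths to achieved MAP or vasopressor dose in the same arm. That matters here because the Background concedes that individualised targets may raise vasopressor use, and the Safety assessment section prespecifies arrhythmic and ischaemic events.

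What is at stake is the board's ability to protect participants at its one scheduled look.

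**Working it through.** **1. The plan's own figures.** Inputs from the Sample size section: 20% control mortality, 6-point reduction (so 14%), two-sided alpha 0.05, power 80%, 2.5% attrition.

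- Pooled rate = (0.20 + 0.14)/2 = 0.17.
- n per arm = [1.96 × √(2 × 0.17 × 0.83) + 0.8416 × √(0.20 × 0.80 + 0.14 × 0.86)]² / 0.06² = 614.1, rounded up to 615.
- Total 1230; 1230/0.975 = 1262 after rounding up. This reproduces the stated 1260 to within rounding and choice of formula; the unpooled-variance version gives 1256.
- 10%, 25% and 50% of 1260 are 126, 315 and 630, as stated.

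**2. Size of difference that is nominally significant at the DSMB look.** Assume 315 per arm (1:1 allocation), complete outcomes and a crude comparison.

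- At 17% pooled mortality: 1.96 × √(2 × 0.17 × 0.83/315) = 0.0587, or 5.9 points.
- At 20% (no effect at the design control rate): 1.96 × √(2 × 0.20 × 0.80/315) = 0.0625, or 6.2 points.
- At 9.5% (average of the 13% and 6% seen in the feasibility study): 1.96 × √(2 × 0.095 × 0.905/315) = 0.0458, or 4.6 points.

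The section gives no interim significance rule for mortality, so these figures are a yardstick and not a boundary.

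**3. What the board would see at the design rates.** Expected deaths are 0.20 × 315 = 63 and 0.14 × 315 = 44.1. Then z = 0.06/√(2 × 0.17 × 0.83/315) = 2.00, two-sided P about 0.045.

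| Truth | Standard | Individualised | Table shown to the board |
|---|---|---|---|
| Benefit | 63 | 44 | 63 v 44 under A/B |
| Harm | 44 | 63 | 63 v 44 under A/B |

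The last column is the same in both rows. Prior rates do not settle it: the design assumes 20% under standard care, but the feasibility study cited in the same section had 13%. Either column could plausibly be the control arm.

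**4. Whether the other table helps.** MAP deficit would probably identify the individualised arm among G and F. That knowledge does not carry to A and B without a key.

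**The case against.** **The article condenses a full protocol, and a DSMB charter may allow unmasking on request.** This is possible, and the text does not say that the labels can never be linked; that is inferred from their being different with no key mentioned. But the point does not rest on an omission. The article states that the board remains blinded, and a charter that says otherwise would contradict it.

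**The labels for serious adverse events are unstated.** If they shared the separation labels, the board could set those events against MAP, and deaths recorded among them might hint at direction. Unequal arm sizes might also link the sets by accident. Neither is a planned safeguard.

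**Coded interim reports are a common choice.** This stands. Coding is not the fault. The fault is two codes with no stated key.

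A reader might infer more than the document supports:

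- *Investigators see safety results by arm at 126 and 315 patients.* The steering group is indeed made up of the trial's own people: "The trial steering group comprising of the chief investigator, medical co-investigators and project co-managers oversees trial governance". But the study team is said to stay blinded, and nothing says that these reviews are by arm.
- *The board can look only once.* A further interim analysis is available if consensus fails, and the DSMB section refers to periodic data.
- *Prespecified adverse events are filtered out by local judgement.* The exemption for "those events that are deemed part of the natural course of the primary illness or expected complications of the critical illness" concerns serious adverse event reporting. The Safety assessment section has the prespecified events reported, and Table 5 tabulates them by arm.
- *The absence of a scheduled DSMB look before 630 patients is an error.* It is a design choice on which practice varies.

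**Conclusion.** The point holds for the labelling and masking of the DSMB's data. As written, a board that must recommend on early termination could see a difference of about 5.9 points or more (nominal P of 0.05 at 17% pooled mortality; 4.6 to 6.2 points for pooled mortality from 9.5% to 20%) without knowing whether it is harm or benefit.

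This assumes 315 patients per arm with complete outcomes, a crude comparison, and no unmasking route in documents not shown. The figures show what could be hidden, not how likely a wrong recommendation is. The defect impairs safety review and should be corrected before the 630-patient look.

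**What to change.** Amend the Interim analyses section and the DSMB charter as follows.

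1. Use one coded label pair in every closed-report table: 14-day mortality, serious and prespecified adverse events, MAP separation and vasopressor dose.
2. Have the report statistician hold the key and release it to the DSMB on request. The Blinding section has the analysing statistician stay blinded, so the key-holder should be someone else, or that section should be reworded.
3. Limit the statement about remaining blinded to the study team.
4. State that the steering team's adverse event reviews at 126 and 315 patients are pooled across arms.

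**Cost:** a text and charter change while recruitment is under way. Sample size, final analysis and number of looks stay the same. The downside is that MAP data under a common label will in effect unmask the DSMB, which is acceptable for an independent board. Whether the DSMB should also review data before 630 patients can be left to the sponsor and the board.

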### Subgroup analyses

Subgroup analyses for the between-group difference in 14-day mortality, specific to each subgroup, will be conducted (Fig. 4). Pre-specified subgroups will be as follows: age 65 years or less *vs.* greater than 65 years, males *vs.* females, Australian *vs.* non-Australian region, hypertensives vs. non-hypertensives, presence of acute kidney injury *vs.* no acute kidney injury, presence of cardiovascular comorbidities vs. no cardiovascular comorbidities at randomisation, invasive vs. non-invasive mechanical ventilation, and cardiogenic shock *vs.* non-cardiogenic shock at randomisation.

**Fig. 4 Fig4:**
[figure not shown]
Example of presentation of results for the subgroup analysis for 14-day all-cause mortality as a forest plot

### Missing data or incongruent data

Medical records will be used to ascertain all outcomes. Outliers will be interrogated for validity and impact explored via sensitivity analyses. The intention to treat population for the primary and secondary outcomes is all participants as randomised. It is expected that there will be no, or minimal, missing data for the outcomes. Analysis of outcomes will be complete case analysis and is expected to include the entire intention to treat population or very close to the entire population. MAP and percentage MAP deficit may be missing for some timepoints, but the method of analysis for MAP and percentage MAP deficit does not require all observations to be non-missing. Missing APACHE III score, type of shock and site data is not anticipated. The proportion of data defining the subgroups is also expected to be complete or nearly complete and patients with missing data will not be included in any subgroup analysis. To minimise loss to follow-up, each site will designate a coordinator responsible for outcome tracking, and outcome data will be obtained from hospital records or national mortality registries where required.

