### Outcomes

The primary outcome is 14-day all-cause mortality. Mortality will be a binary variable, with mortality defined as a record of death within 14 days after randomisation.

Secondary outcomes (Table 3) are:90-day all-cause mortality: All-cause mortality from randomisation to day 90.Time to death through day 14: Time to death (hours) will be calculated as the difference between the date and time of death and the date and time of randomisation if death occurs within 14 days of randomisation. Where exact time of death is not available, time will be assumed as 12:00 on the date of death.Time to death through day 90: Time to death (days) will be calculated as the difference between the date of death and the date of randomisation.Major Adverse Kidney Event (MAKE-14): MAKE-14 is defined as a composite measure of death, new initiation of RRT, or doubling of serum creatinine from the premorbid level at day 14 [13, 14]. Individual components of MAKE-14 will also be reported. The premorbid serum creatinine level will be sourced as the latest available value from medical records within the last year before hospital admission or, if this value was unavailable, as the latest available value during the hospital stay at least 7 days before ICU admission. When neither of these are available, the premorbid serum creatinine will be estimated following the Kidney Disease: Improving Global Outcome (KDIGO) guidelines as described previously [15].Renal Replacement therapy (RRT) free days until day 28: Number of days from randomisation to day 28 where the participant is both alive and not dependent on RRT. Patients who die within 28 days will be assigned the worst score of − 1.

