### Primary outcome

Effect estimates for 14-day all-cause mortality will be derived from multivariable logistic mixed effects models with a random intercept for site (assumed normally distributed on the logit scale, with a constant variance) to account for clustering within sites and fixed effects for treatment group, time between T0 (initiation of vasopressor therapy) and randomisation, APACHE III score at randomisation, noradrenaline-equivalent dose at randomisation and type of shock (Table 4). A two-sided *P*-value for the effect of treatment will be obtained from this model and values < 0.05 will be considered statistically significant. The effect estimates of interest will be the relative risk and risk difference (individualised care versus standard care). The relative risk estimate will be obtained as a ratio of the mean for each group of the individual predicted probabilities obtained from the logistic regression model. Differences of these means will be the risk difference. Bootstrapping, using 10,000 iterations, will be used to calculate 95% confidence intervals.

**Table 4 Tab4:** Outcome measures

	Standard MAP (*n* = xxx)	Individualised MAP (*n* = xxx)	Adjusted^*^ relative risk (95% CI)	Adjusted^*^ risk difference (95% CI)	*P* value
Day 14 all-cause mortality, *n* (%)					
Major Adverse Kidney Event^δ^ within 14 days of randomisation, *n* (%)					
- New requirement for RRT					
- Doubling of creatinine					
RRT- free days^#^ by day 28, *n* (%)					
Day 90 all-cause mortality, *n* (%)					

*RRT* renal replacement therapy

^*^ The model included random intercepts for sites and fixed effects for treatment group, the time between T0 (initiation of vasopressor therapy) and randomisation, APACHE III score at randomisation, vasopressor dose at randomisation and type of shock

^**δ**^ Major adverse kidney event (MAKE)−14 was a composite outcome of death, or new renal replacement therapy during the first 14 days, or doubling of serum creatinine from pre-illness level on day 14 or on day of discharge from ICU, whichever was earlier

^#^ Patients who died were assigned the worst score of − 1

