### Sensitivity analyses

Impact of any missing outcomes for day 14 and day 90 mortality will be assessed using imputed outcomes under best–worst and worst-best case scenarios. In the best–worst scenario, a “best” outcome event (i.e. did not die) will be assigned in place of all missing outcomes in one treatment arm, and a “worst” outcome event (i.e. died) in place of all missing outcomes in the other treatment arm. The worst-best scenario will be the opposite assignment of outcomes. If the conclusions are similar for these two scenarios, then no missing data analyses will be conducted. However, if conclusions are substantively different, then a multiple imputation analysis will be performed, where missing outcomes will be imputed using chained equations and predictive mean matching, using the five nearest neighbours, in each of the study arms.

Other sensitivity analyses including *per protocol* analysis and *as treated* analysis, based on management of MAP targets during the first 48 h of vasopressor or inotrope therapy post randomisation, will also be conducted. For per protocol analysis, those patients who were not able to be managed as per the specified protocol for the allocated arm will be excluded from each group. For as treated analysis, patients will be grouped into study arms according to the protocol of the study arm that was followed. Determinative thresholds for protocol non-compliance for the control arm will be the mean achieved MAP greater than 75 mmHg and mean MAP-deficit < 8% and mean noradrenaline-equivalent dose > 0.10 mcg/kg/min during the first 24 h of the study period. Whereas determinative thresholds for protocol non-compliance for the intervention arm will be the mean achieved MAP less than 75 mmHg and mean MAP-deficit of 8% or more and mean noradrenaline-equivalent dose < 0.15 mcg/kg/min during the first 24 h of the study period.

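### Complete-case analysis of MAKE-14 can drop only patients alive and free of RRT, so arm risks tend to be overstated and the risk difference can be biased in either direction

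*Protocol article*

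**What the plan says.** - **Missing-data rule** (Missing data or incongruent data): "Analysis of outcomes will be complete case analysis and is expected to include the entire intention to treat population or very close to the entire" randomised set. The same paragraph defines the intention-to-treat population for primary and secondary outcomes alike and justifies the rule by expectation: "It is expected that there will be no, or minimal, missing data for the outcomes".
- **Endpoint** (Outcomes): MAKE-14 is a "composite measure of death, new initiation of RRT, or doubling of serum creatinine from the premorbid level at day 14". The footnote to Table 4 words the creatinine component differently: "doubling of serum creatinine from pre-illness level on day 14 or on day of discharge from ICU, whichever was earlier".
- **Baseline creatinine** (Outcomes): this has a fallback. "When neither of these are available, the premorbid serum creatinine will be estimated".
- **Model** (Secondary outcomes): MAKE-14 is analysed in the same way as 14-day mortality, giving a relative risk and a risk difference from a logistic mixed model.
- **Checks on missing outcomes** (Sensitivity analyses section): "Impact of any missing outcomes for day 14 and day 90 mortality will be assessed using imputed outcomes under best–worst and worst-best case scenarios". The multiple imputation that may follow belongs to the same mortality check. MAKE-14 is not named.

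**The concern.** Few or no missing values is a reasonable expectation for vital status, which hospital records and national mortality registries can supply. It is less secure for a composite with one component that needs a creatinine on a named day. A mortality registry holds no creatinine, and Table 1 schedules peak creatinine after randomisation but no day-14 sample.

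A patient who dies or starts RRT is a MAKE-14 event whatever the creatinine, and the premorbid value can be estimated. Only the follow-up creatinine can therefore leave MAKE-14 unknown, and only in a patient who is alive and RRT-free. A complete-case analysis keeps every death and RRT event and loses patients only from the rest. That is selection on the outcome, and it departs from the all-randomised population that the plan says it analyses.

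MAKE-14 is the first secondary endpoint listed in the abstract and part of the trial hypothesis. The outcome best protected against missing data has sensitivity analyses, and the one most exposed has none stated.

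**Working it through.** **Plan's own figure.** With 20% v 14%, two-sided alpha 0.05 and 80% power, the usual two-proportion formula without continuity correction gives 615 per arm, 1230 in total. Then 1230 / (1 − 0.025) = 1262, against the stated 1260. The mortality inputs reproduce. The article states no MAKE-14 risk and no share of missing creatinine.

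**Notation**
- d = risk of death or new RRT. The plan's 20% v 14% mortality is used as a stand-in (assumption).
- q = risk of creatinine doubling among patients alive and RRT-free (assumption).
- m = share of those patients with no usable follow-up creatinine (assumption).
- q_m = doubling risk among those with a missing value; equal to q if values are missing at random within this group.

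True risk = d + (1 − d)q

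Complete-case risk = [d + (1 − d)(q − m·q_m)] / [1 − (1 − d)m]

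Risk differences (RD) are standard minus individualised, in percentage points, without covariate adjustment.

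**A. Effect on death/RRT only, equal m, q = 10% in both arms.** True risks are 0.20 + 0.80 × 0.10 = 28.0% and 0.14 + 0.86 × 0.10 = 22.6%; RD 5.40.

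| m | Standard | Individualised | RD | RD ratio |
|---|---|---|---|---|
| 2.5% | 28.4% | 22.9% | 5.49 | 1.02 |
| 5% | 28.7% | 23.2% | 5.58 | 1.03 |
| 10% | 29.6% | 23.8% | 5.78 | 1.07 |
| 20% | 31.4% | 25.2% | 6.21 | 1.15 |
| 30% | 33.7% | 27.0% | 6.70 | 1.24 |
| 40% | 36.5% | 29.2% | 7.26 | 1.34 |

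Example at m = 30%: standard (0.20 + 0.80 × 0.70 × 0.10) / (1 − 0.80 × 0.30) = 0.256 / 0.760 = 33.7%; individualised (0.14 + 0.86 × 0.70 × 0.10) / (1 − 0.86 × 0.30) = 0.2002 / 0.742 = 27.0%. The RD ratio does not depend on q when q is equal in both arms. With q = 5% and m = 30%, risks read 30.0% v 22.9% instead of 24.0% v 18.3%.

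The relative risk hardly moves: 22.6 / 28.0 = 0.81 in truth, and 27.0 / 33.7 = 0.80 at m = 30%.

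**B. Effect on doubling only, equal m** (d = 20% in both arms, q = 15% v 9%). The true RD of 4.80 becomes 4.75 (m = 5%), 4.70 (10%), 4.57 (20%) and 4.24 (40%). The RD is attenuated, although both arm risks rise.

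**C. Unequal m** (d = 20% v 14%, q = 10%; true RD 5.40). With 5% missing in the standard arm and 10% in the individualised arm, RD = 4.96. With the shares reversed, RD = 6.40.

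**D. No true effect** (d = 20%, q = 10% in both arms). Missing shares of 5% v 10% create a false RD of 0.8 point, and 10% v 20% create 1.9 points (31.4% − 29.6%, before rounding). The sign depends on which arm loses more.

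**E. Dropped patients at higher risk** (m = 10%, q = 10%, q_m = 40%). Arm risks fall, from 28.0% and 22.6% to 27.0% and 21.0%.

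**The case against.** The strongest reply is that little will be missing. Under the Table 4 footnote, a patient who leaves ICU early is assessed on the day of ICU discharge, so the obvious source of missing values, recovered patients who have gone before day 14, largely disappears. What remains is patients with no test on that day. Each site also has a coordinator tracking outcomes, hospital records are a source, and MAKE-14 components are reported separately. At m of 5% or less in both arms, the bias is trivial. This stands as far as size goes. However, the Outcomes section says day 14 without the ICU-discharge alternative, and under that reading the larger shares are plausible.

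A reader might infer that the complete-case rule inflates the risk difference as such. The document does not support that. Inflation needs roughly equal missingness and an effect mainly on death or RRT. The hypothesis also expects a benefit on kidney events, and cases B and C show attenuation. An effect on both components gives less inflation: with doubling at an assumed 10% v 7% alongside 20% v 14%, it is about 4% at m = 10% and 14% at m = 30%. Even overstated arm risks need the dropped patients to be at lower risk than their arm (case E).

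It can also be said that an article leaves such handling to a fuller plan. But the complete-case rule is stated here, for outcomes in general, in an article that says it publishes the pre-specified analysis plan. The point concerns a rule that is fixed, not an omitted detail.

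**Conclusion.** The concern holds in limited form. The stated rule reaches MAKE-14 and can exclude only patients alive and RRT-free, and no stated analysis tests the effect. Overstated arm risks are the natural expectation if those dropped are mainly recovered patients. The direction of bias in the risk difference cannot be predicted, and the relative risk is little affected when missingness is equal.

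The size rests on assumed missing shares, on mortality standing in for death or RRT, and on unadjusted arithmetic. It is negligible at an equal 5% or less. It becomes material at 10% to 30% or when the arms differ, and such shares are plausible mainly if creatinine is required on day 14 itself. Figures at the upper end should not be read as a forecast. The case for change is that the bias is unpredictable, untested and cheap to prevent.

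**What to change.** 1. Reconcile the Outcomes section with the Table 4 footnote so that the creatinine component has one stated time point.
2. In the missing-data section, exempt MAKE-14 from complete-case analysis and leave the rule in place for the other outcomes, so that RRT-free days still has one. Keep every randomised patient with known death and RRT status. Where the follow-up creatinine is missing, multiply impute that component within arm from creatinine at randomisation, peak creatinine and the model covariates.
3. In the sensitivity analyses, extend the best–worst and worst–best scenarios to MAKE-14, assigning doubling or no doubling to patients whose creatinine component is missing.

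Substituting the last creatinine before hospital discharge is not advised, because it would add a third time point and partly redefine the endpoint.

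The cost is wording and a little more programming, using variables already collected. The imputation relies on creatinine being missing at random given those variables, and the extended scenarios bound the consequences if it is not. The trial is still recruiting, so the change can be made before database lock.

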## Statistical methods

Analyses will be carried out by a biostatistician using standard statistical software (SAS, Stata and/or R). All randomised patients will be included in an intention-to-treat analysis. Baseline characteristics (Table 2) and other process of care variables (Table 3) will be tabulated for both groups and reported as mean (± standard deviation or median (interquartile range) for continuous variables and as count (%) for categorical variables.

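### The complete-case rule, applied to covariate-adjusted models, drops randomised patients whose outcome is known if a baseline covariate is missing; the likely effect is small and one sentence removes it

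*Protocol article*

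**What the plan says.** Four parts of the Protocol article bear on this.

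- **Analysis set.** Statistical methods: "All randomised patients will be included in an intention-to-treat analysis". The section on missing data repeats it: "The intention to treat population for the primary and secondary outcomes is all participants as randomised".
- **Missing-data rule.** The same section continues: "Analysis of outcomes will be complete case analysis". It expects this to cover all, or nearly all, of the intention-to-treat population. On covariates it says only: "Missing APACHE III score, type of shock and site data is not anticipated". It gives no rule in case such data are missing after all, and it does not mention noradrenaline-equivalent dose or time from T0.
- **Model.** Under Primary outcome, the fixed effects besides treatment are "time between T0 (initiation of vasopressor therapy) and randomisation, APACHE III score at randomisation, noradrenaline-equivalent dose at randomisation and type of shock", with a random intercept for site. "A two-sided *P*-value for the effect of treatment will be obtained from this model", and the relative risk and risk difference are derived from its predicted probabilities. Under Secondary outcomes, 90-day mortality and MAKE-14 are analysed in the same way, and the Cox models and the proportional odds model for RRT-free days use the same set of covariates.
- **Sensitivity analyses.** "Impact of any missing outcomes for day 14 and day 90 mortality will be assessed using imputed outcomes" under best-worst and worst-best scenarios. Multiple imputation follows only if those two scenarios lead to different conclusions, and it too is described for outcomes only.

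**The concern.** A regression fitted to complete cases needs the outcome and every covariate. Under the stated rule a patient with a recorded death or survival at day 14, but without (say) an APACHE III score, contributes nothing to the primary P-value, relative risk or risk difference. No later step brings that patient back. The imputation covers outcomes, and the outcome table lists adjusted effect estimates only.

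Deaths are to be found in hospital records or, where required, national mortality registries, so outcome data should be nearly complete. Any loss from the primary analysis may then come mainly through the covariates, the one route for which the article has no rule. At stake are a modest loss of information, a gap between the stated and the actual analysis set, and a choice of method left open until the data are in hand.

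**Working it through.** **1. Does the text imply the exclusion?** Set side by side: all randomised patients are to be analysed; outcome analyses are complete case; the primary test comes from a model with four baseline covariates; imputation is for outcomes only. A patient with a known outcome and one missing covariate belongs to the first set but cannot enter the model under the second and third statements, and the fourth does not help. The trigger for imputation depends on missing mortality data. If mortality is complete and some covariates are not, the two scenarios coincide and imputation never starts.

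**2. Which covariates could be missing?**
- Site is known for everyone, since randomisation is stratified by site.
- Time from T0 should rarely be missing, because eligibility requires less than 24 h since vasopressor or inotrope start.
- Vasopressor dose is scheduled at baseline in Table 1.
- APACHE III and type of shock are expected to be complete.

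The article gives no missingness rate, so any rate used below is an assumption.

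**3. Reproduce the planned sample size.** Inputs from Sample size: 20% v 14%, alpha 0.05 (two-sided, from Primary outcome), power 80%, attrition 2.5%. With mean proportion 0.17,

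n per arm = [1.960 × √(2 × 0.17 × 0.83) + 0.842 × √(0.20 × 0.80 + 0.14 × 0.86)]² / 0.06²
= [1.960 × 0.5312 + 0.842 × 0.5295]² / 0.0036 = 614.1, rounded up to 615.

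The total is 1230, and 1230 / 0.975 = 1262, against 1260 stated. The planned figure reproduces.

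**4. Power with covariate losses.** With n per arm,

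power = Φ[(0.06 × √n − 1.960 × 0.5312) / 0.5295].

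After 2.5% attrition, n = 630 × 0.975 = 614.25. If a share m of these patients lacks a covariate, n = 614.25 × (1 − m).

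| Assumed m | n per arm | Power after 2.5% attrition | Power if there is no outcome attrition (n = 630 × (1 − m)) |
|---|---|---|---|
| 0 | 614.25 | 80.0% | 81.0% |
| 2% | 601.97 | 79.2% | 80.2% |
| 2.5% | 598.89 | 79.0% | 80.0% |
| 5% | 583.54 | 78.0% | 79.0% |

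At 2% to 5%, the patients dropped despite a known outcome number 1228.5 × 0.02 = 25 to 1228.5 × 0.05 = 61. If no outcomes are missing, the range is 1260 × 0.02 = 25 to 1260 × 0.05 = 63.

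This is the unadjusted two-proportion calculation that reproduces the plan's own figure. It takes no account of any precision gained from the covariates or of clustering by site, and it treats the losses as equal in the two arms.

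**The case against.** The strongest reply is that the statement about all randomised patients gives the principle and the missing-data section gives its implementation, which is openly qualified, because that section itself allows that a few patients may not be covered. Further, the complete-case wording is attached to outcomes; the loss through covariates follows from fitting an adjusted model and is not spelled out. The covariates are tied to eligibility, scheduled at baseline or expected to be complete. If outcomes are complete, the 2.5% allowance absorbs 2.5% covariate missingness, leaving power at 80.0%. Finally, a supplement exists that is not shown and may hold a rule for covariates.

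Much of this stands. It limits the size of the problem and rules out calling it a serious contradiction. It does not remove the point. The article describes itself as carrying the pre-specified analysis plan, fixes the complete-case rule itself, and takes up covariate missingness in the same paragraph without saying what happens if the expectation fails. The log-rank tests need no covariates and would keep these patients, but they serve secondary outcomes and give no risk estimate.

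A reader might infer two stronger things. One is that the plan breaks intention to treat. The documents do not support that: patients are analysed as randomised, near-complete inclusion is expected, and exclusions arise only if a covariate is missing. The other is that patients who die early are the likely ones to have incomplete scores, so that the loss would bias the comparison. Nothing in the article says so, and the model uses the APACHE III score at randomisation.

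**Conclusion.** The point holds as a minor defect. Read with the adjusted models, the stated rule would drop a patient whose outcome is known for want of a baseline value, which is less than the inclusion of all randomised patients promised under Statistical methods, and no planned sensitivity analysis examines such exclusions. The effect is nil with complete covariates. Under an assumed 2% to 5% missing, in addition to 2.5% attrition, the cost is about 1 to 2 points of power (80.0% to 79.2% or 78.0%). The sample size itself is sound. The documents give no basis for claiming bias in a particular direction.

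**What to change.** In the section on missing data, limit complete case to the outcome and add a rule for covariates. For example: in all adjusted models, a missing baseline covariate is replaced by the mean (continuous) or most frequent category (categorical) over both arms combined, without reference to treatment arm or outcome, so that every randomised patient with a known outcome is analysed; the number of values filled is reported by arm.

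The covariates describe the patient at randomisation, so filling them without regard to arm does not disturb the randomised comparison. Multiple imputation of the covariates would also be acceptable; what matters is that the rule is fixed before the data are examined. The cost is one sentence and trivial programming. Recruitment is expected to run to 2028, so there is time to make the change well before database lock.
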